## Abstract

**Background:**

Quitting smokers gain weight. This deters some from trying to stop smoking and may explain the increased incidence of type 2 diabetes after cessation. Dieting when stopping smoking may be counterproductive. Hunger increases cravings for smoking and tackling two behaviours together may undermine quitting success. A meta-analysis of randomized controlled trials (RCTs) showed individualized dietary support may prevent weight gain, although there is insufficient evidence whether it undermines smoking cessation. Commercial weight management providers (CWMPs), such as Slimming World, provide individualized dietary support for National Health Service (NHS) patients; however, there is no evidence that they can prevent cessation-related weight gain.

Our objective is to determine whether attending Slimming World from quit date, through referral from NHS Stop Smoking Services, is more effective than usual care at preventing cessation-related weight gain.

**Methods:**

This RCT will examine the effectiveness of usual cessation support plus referral to Slimming World compared to usual cessation support alone. Healthy weight, overweight and obese adult smokers attending Stop Smoking Services will be included. The primary outcome is weight change in quitters 12 weeks post-randomization. Multivariable linear regression analysis will compare weight change between trial arms and adjust for known predictors of cessation-related weight gain.

We will recruit 320 participants, with 160 participants in each arm. An alpha error rate of 5% and 90% power will detect a 2 kg (SD = 2.5) difference in weight gain at 12 weeks, assuming 20% remain abstinent by then.

**Discussion:**

This trial will establish whether referral to the 12-week Slimming World programme plus usual care is an effective intervention to prevent cessation-related weight gain. If so, we will seek to establish whether weight control comes at the expense of a successful quit attempt in a further non-inferiority trial.

Positive results from both these trials would provide a potential solution to cessation-related weight gain, which could be rolled out across England within Stop Smoking Services to better meet the needs of 0.75 million smokers stopping with NHS support every year.

**Trial registration:**

Current Controlled Trials ISRCTN65705512

## Background

Weight gain is a well known consequence of smoking cessation [1,2]. It may deter smokers from attempting to quit [3] and offsets some advantages of giving up smoking. Smoking cessation-related weight gain partly explains the finding that the incidence of type 2 diabetes is increased by up to 73% in the years after cessation [4-6] and there is a 30% increased risk of hypertension [7] compared to continuing smoking. Quitters who gain weight have less improvement in lung function than those who avoid weight gain [8].

An ideal intervention to prevent weight gain would begin at the time of quitting, because weight gain is most rapid initially and then the rate of gain slows [9,10]. Qualitative findings suggest that, in the overweight population, at least, waiting until a quit attempt is established before addressing weight is unacceptable [11].

However, preventing weight gain early in cessation is controversial. The main reason quit attempts fail is due to quitters succumbing to their cravings to smoke. Evidence suggests that hunger increases urges to smoke [12,13] and people who gain most weight are more likely to succeed in quitting smoking [14]. This suggests that avoiding hunger and ameliorating cigarette cravings with food may enhance smoking abstinence and this has become standard advice on how to quit, with healthy food choices often advocated.

We investigated the effectiveness of different interventions to prevent weight gain during cessation in a recent Cochrane review update [15]. General dietary education to reduce energy intake through eating a low fat, healthy diet and increasing exercise did not prevent weight gain compared to standard smoking cessation behavioral support. Furthermore, there was a statistically significant reduction in abstinence at 12 months (Table 1). However, an individually tailored plan to reduce energy intake and increase exercise, with regular monitoring and adaptation of individual goals, reduced weight gain at 6 and 12 months without a statistically significant reduction in abstinence rates (Table 1), although the sample size is too small to be conclusive.

**Table 1 T1:** Effects of dietary interventions on weight change and abstinence during smoking cessation

**Intervention compared to standard smoking cessation**	**Mean difference in weight change (kg (95% CI))**		**Abstinence (RR (95% CI))**	
	**End of treatment**	**At 12 months**	**End of treatment**	**At 12 months**
General lifestyle and calorie reducing dietary advice	−0.04 (−0.57, 0.50)	−0.21 (−2.28, 1.86)	0.90 (0.76, 1.06)	0.66 (0.48, 0.90)
Individually tailored dietary and lifestyle advice	−1.11 (−1.93, −0.29)	−2.58 (−5.11, −0.05)	1.11 (0.84, 1.46)	0.74 (0.39, 1.43)

CI, confidence interval; RR, risk ratio.

Commercial weight management providers (CWMPs) offer this type of individually tailored dietary and exercise plan. They have already been shown to be an effective way for people to achieve successful weight loss through referral from NHS primary care [16]. Therefore referral to a CWMP on prescription from the National Health Service (NHS) Stop Smoking Services may be an effective way to prevent smoking-related weight gain without a detrimental effect on quitting success. The first step to investigating this is to run a trial to assess whether this is an effective way to prevent weight gain during smoking cessation.

We will use the results of such a trial to inform a larger trial powered to investigate non-inferiority on smoking cessation rates. This will assess whether weight control comes at the expense of a successful quit attempt. This trial would require over 1,100 participants and is premature without first showing that the intervention can reduce weight gain, which is what we propose here. We will seek further funding for the larger trial to investigate effects on abstinence if the intervention reduces weight gain.

## Methods

### Design

This is an open label, phase II, randomized controlled trial (RCT) to compare standard stop smoking behavioral support with an intervention that will, in addition to providing standard stop smoking support, include personalized weight management support, provided by Slimming World.

This is an open label trial, so blinding patients and smoking cessation advisors to allocation to intervention or control is impossible. The primary outcome is objectively measured weight and therefore the scope for bias is limited. Stop smoking advisors, who will weigh participants, will not provide the weight control support and are unlikely to have a vested interest in interpreting weight change favorably. In addition, they will be required to follow a protocol that specifies outdoor coats and shoes only are removed before weighing.

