#### Research team decision to withdraw

The intervention is based on the principles of healthy eating and we do not expect any adverse effects. Standard practice within the intervention is to monitor weight and provide feedback, and therefore an unhealthy rate of weight loss is unlikely to occur for long without correction. In the event that a participant develops a condition in which dietary energy restriction is ill-advised, for example embarking on a course of chemotherapy, they will be withdrawn from treatment. Data up to the time of withdrawal from treatment will be used unless the participant requests otherwise. Before beginning the trial, participants will have to consent to notifying the research team of such a change in medical history which is detailed on the consent form. We will ask the participant’s general practitioner to notify the research team of such changes in medical history.

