#### Session 6: week post-quit (week +4)

This is typically the last visit to the Stop Smoking Service and when 4-week abstinence will be assessed. Weight will be measured and the EQ-5D will be completed by all participants at this visit.

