### Intervention

CWMPs are available ‘on prescription’ through general practices and provide 12 weeks of free membership of the group-based weight management class. There are three main providers offering services to the NHS: Rosemary Conley, Slimming World and Weight Watchers; the cost of a 12-week course to the NHS is about £60. Each of these providers are potentially suitable and their interventions have been described elsewhere [16]. In brief, each provides goal setting for weight, regular monitoring, and a tailored energy restriction using a either a food points system (Weight Watchers), food portion measures (Rosemary Conley), or controlled amounts of high energy foods and personal eating plans (Slimming World).

For this trial, we are using Slimming World, since this provider has been successful at improving health and reducing health risks associated with specific medical conditions through referral schemes within particular patient populations, some of which are designed to prevent excessive weight gain rather than focus on weight loss, for example during pregnancy [22,23]. Such an approach is particularly pertinent to quitting smokers who need to prevent cessation-related weight gain.

In addition to usual care, participants will be given a referral form for Slimming World when they attend their pre-quit visit. The stop smoking advisor will discuss times and locations of local group meetings, and attendance at a convenient group will be agreed. The participant will attend weight management sessions from their quit day (or as near to that date as possible). They will attend Slimming World for 12 weeks receiving support to lose weight or prevent weight gain. The choice of modest weight loss or weight gain prevention will depend upon whether a participant wants to lose weight or not, and whether or not the participant is overweight or obese at baseline.

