### Control

Participants are encouraged to quit smoking first, before tackling weight. Stop smoking advisors can advise satiating hunger with healthy foods, but they will not provide detailed or personalized advice on weight and will not set weight targets.

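### The weighing rule does not standardise the clothing that stays on, so in this open-label trial a modest dress-related bias towards the intervention at week 12 cannot be excluded

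*Protocol article*

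**What the plan says.** The Design section states that "blinding patients and smoking cessation advisors to allocation to intervention or control is impossible". It then argues that "The primary outcome is objectively measured weight and therefore the scope for bias is limited", and supports this in two ways. The advisors who do the weighing "will not provide the weight control support and are unlikely to have a vested interest in interpreting weight change favorably", and "they will be required to follow a protocol that specifies outdoor coats and shoes only are removed before weighing". The Primary outcome measure section adds that advisors are trained in measurement and that each clinic keeps to one set of scales throughout.

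The arms differ in how much attention weight receives. The Intervention section says of the commercial providers, Slimming World included, that "each provides goal setting for weight, regular monitoring, and a tailored energy restriction". The section on withdrawal by the research team says "Standard practice within the intervention is to monitor weight and provide feedback". For controls, the Control section says of the advisors that "they will not provide detailed or personalized advice on weight and will not set weight targets".

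The trial itself weighs both arms. Baseline measures come before randomization (Session 2). At week 4, "Weight will be measured and the EQ-5D will be completed by all participants at this visit", and weight is measured again at week 12 (Session 7).

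**The concern.** The safeguards in the article deal with the observer and the instrument: advisors without a stake in the result, training, constant scales and a common removal rule. None deals with what an unblinded participant chooses to wear to a booked weighing. The rule lists two items to come off and says that only these do. It leaves jumpers, other indoor layers and belts in place, and is silent on pockets.

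At baseline this can only add noise, because nobody yet knows their arm. At week 12, one arm has had weight goals, monitoring and feedback and the other has not. If dress differs by arm at that visit, the more plausible direction is lighter dress in the intervention arm, which would count as prevented weight gain. The article does not say that clothing is recorded, so the analysis could not be expected to detect or adjust for it.

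The week-12 result also drives later decisions. The 26-week follow-up happens only if week 12 shows a difference in mean weight (Session 8). Funding for the larger non-inferiority trial will be sought only if the intervention reduces weight gain (Background).

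**Working it through.** **Inputs from the Sample size section:** difference 2 kg, SD 2.5 kg, alpha 5% (sidedness not stated; two-sided assumed), power 90%, about 32 abstainers per arm, 20% abstinent at 12 weeks. **Input not in the documents:** the mean between-arm difference in clothing weight at week 12, written *b*. It is an assumption, varied from 0 to 0.5 kg.

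**1. The plan's own figure.** n per arm = 2 × (1.960 + 1.282)² × 2.5² / 2² ≈ 32.8, so 33 by the normal formula and 34 by the exact t calculation. At 32 per arm, power is 89.3% (normal) or 88.3% (t). 32 / 0.20 = 160 per arm, 320 in total. The stated size is reproduced closely enough, and nothing below calls for changing it.

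**2. Precision of the comparison.** SE = 2.5 × √(2/32) = 0.625 kg. The smallest difference that reaches two-sided 5% significance is t(0.975, 62 df) × 0.625 ≈ 1.25 kg.

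**3. Effect of a clothing shift when the intervention does nothing.** The t statistic then has noncentrality b / 0.625 on 62 df.

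| Assumed b (kg) | b / 0.625 | Share of 2 kg target | Rejects in favour of intervention | Rejects, two-sided |
|---|---|---|---|---|
| 0 | 0 | 0% | 2.50% | 5.00% |
| 0.2 | 0.32 | 10% | 5.00% | 6.14% |
| 0.3 | 0.48 | 15% | 6.85% | 7.60% |
| 0.5 | 0.80 | 25% | 12.05% | 12.35% |

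**4. Effect on the estimate.** The shift adds directly: with b = 0.5 kg, a true difference of 1.5 kg would be read as 2.0 kg. Against the smaller 1.11 kg end-of-treatment effect for individually tailored advice in Table 1, shifts of 0.2 and 0.5 kg are 0.2/1.11 = 18% and 0.5/1.11 = 45%.

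**5. What the shift cannot do.** Dress alone would have to differ by 1.25 kg on average to reach significance in expectation, and by 2 kg to account for the whole target effect. Even 0.5 kg as a mean is demanding: for example, half of the intervention abstainers would each have to shed 1 kg more than controls.

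**6. Clothing variation unrelated to arm.** This is noise, not bias. Assume an independent clothing SD *s* at each of the two weighings, not already contained in the 2.5 kg. The SD of change is then √(2.5² + 2s²). With s = 0.3 kg it is 2.54 kg and power at 32 per arm is 87.4%. With s = 0.5 kg it is 2.60 kg and power is 85.8%. Both compare with 88.3%, so the loss is small.

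**The case against.** The strongest reply is that the article does have a rule. It is common to both arms and applied by trained people who do not deliver the weight programme. By limiting removal to two items, it stops a keen participant or advisor from taking off more at the scale. Controls are unblinded too, are weighed at the same trial visits, and may also dress lightly. The week-12 weighing takes place at the Stop Smoking Service, so a habit formed at the slimming group need not carry over. No clothing weight is given, and the true shift may be zero. The article also condenses a weighing protocol and training that are not shown.

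Much of this stands, and it limits what can be claimed. A reader might infer that intervention participants are weighed weekly and learn to dress lightly. The documents give no frequency, only regular monitoring with feedback, and say nothing about dress. A reader might call clothing uncontrolled, but a common removal rule is a partial control. A reader might take the bias as certain to favour the intervention, but the documents do not show that dress will differ by arm at all. Nor does the ±0.5 kg maintenance range in the Intervention section help to size the problem: it reassures participants who want only to hold their weight, and is neither an endpoint nor a margin.

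The reply does not remove the central point. The rule is stated, not left out, and its restriction to two items is put forward as protection against bias. A fuller procedure would have to go beyond that wording to cover the clothing that remains. The listed safeguards still address the person weighing and the scales, not the person being weighed.

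**Conclusion.** The point holds in a limited form. The stated rule does not standardise remaining clothing or pocket contents, in a trial where participants know their arm and only one arm receives weight goals, monitoring and feedback. A modest bias towards the intervention on the primary outcome cannot be excluded, and the objectivity of a scale reading does not exclude it.

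Its size is unknown. Over an assumed shift of 0 to 0.5 kg, the two-sided false-positive rate runs from the nominal 5% to about 12%, and the estimate is inflated by up to a quarter of the 2 kg target. This rests on 32 abstainers per arm, SD 2.5 kg and a two-sided 5% t-test. It would be wrong to conclude that dress could produce the planned 2 kg effect, or that the trial is invalid. This is an inexpensive improvement to measurement, not a fatal flaw.

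**What to change.** For participants not yet weighed at baseline, replace the rule with one that fixes what stays on: light indoor clothing, with shoes, coat and heavy outer layers off and pockets emptied. Apply it identically at baseline and at every follow-up, in both arms. Add a CRF tick-box for any departure.

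Recruitment has already begun (Trial status). Participants weighed at baseline under the present rule should therefore stay on it at all their visits, so that their change in weight is not distorted by a switch, and their clothing should be recorded from now on.

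The cost is a short addition to advisor training and to the CRF. The cohort will also contain two weighing rules, each consistent within a participant. Randomization is stratified by advisor in blocks of 2, 4 and 6, so if each advisor changes over on a single date the two rules should fall almost evenly across the arms. Sample size, arms and the primary analysis need no change.

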### Setting

We propose recruiting participants from NHS commissioned Stop Smoking Services within Bristol and North Somerset in the first instance. Participating services located within pharmacies, general practices and community centers will display an A3 poster advertising the trial.

## Participants

### Inclusion criteria

• Daily smokers with expired CO >10 ppm.

• Aged 18 years or over.

• Body mass index (BMI) greater or equal to 23 kg/m^2^. We included participants with an ideal BMI, as well as those who are overweight in the trial. This is because we are not only seeking to help people who are overweight to manage their weight, but also to enable those who are a healthy weight to prevent the weight gain that is associated with smoking cessation. Without engaging in weight management strategies to counteract the physiological and behavioral responses to smoking cessation, 85% of people who quit smoking will gain weight, regardless of their starting BMI [17].

• Willing to be randomized to either the control or intervention arm, and willing and able to comply with the intervention and all study procedures.

• Able to understand and consent to study procedures, assessed at first appointment with the stop smoking advisor.

### Exclusion criteria

• Pregnant smokers.

• BMI <23 kg/m^2^. Mortality has been shown to be lowest in people with a 22 >BMI <25 [18], therefore preventing weight gain in those with lower BMIs may not lead to health gain.

• Any medical condition in which weight loss would be contraindicated, for example current course of chemotherapy.

• Currently losing weight, intentionally or unintentionally.

• Participating in any other intervention trial.

### Withdrawal criteria

#### Participant decision to withdraw from treatment and follow-up

Participants may choose to withdraw from treatment and/or follow-up at any time. Failure to attend treatment visits will not be considered as withdrawal from the whole trial, and these participants will still be contacted for follow-up appointments unless they have requested otherwise. We expect that participants who actively request to withdraw from the trial and no longer be contacted will be fewer than 5% of participants, and as such we will not replace these individuals.

#### Research team decision to withdraw

The intervention is based on the principles of healthy eating and we do not expect any adverse effects. Standard practice within the intervention is to monitor weight and provide feedback, and therefore an unhealthy rate of weight loss is unlikely to occur for long without correction. In the event that a participant develops a condition in which dietary energy restriction is ill-advised, for example embarking on a course of chemotherapy, they will be withdrawn from treatment. Data up to the time of withdrawal from treatment will be used unless the participant requests otherwise. Before beginning the trial, participants will have to consent to notifying the research team of such a change in medical history which is detailed on the consent form. We will ask the participant’s general practitioner to notify the research team of such changes in medical history.

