### Analysis plan

#### Primary analysis

Change in weight between intervention and the control arm of the study will be compared using a *t*-test and then adjusted for known predictors of weight gain after cessation, including stop-smoking medication use, using linear regression analysis. Weight will be analysed in long-term abstainers because only long-term abstainers gain more weight over time than the rest of the population.

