#### Secondary analysis

Abstinence will be analysed on an intention-to-treat basis. This phase II trial is underpowered to detect the difference between abstinence rates in the control and intervention arm. We will calculate the proportion of participants abstinent in each trial arm. Analysis of abstinence rates will assume participants who do not report for follow-up have reverted to smoking, which is standard practice. Quantitative measures of acceptability will be presented as descriptive statistics.

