#### Exploratory outcomes

The association of exploratory outcomes with weight control and quitting success will be examined using regression modeling and on an intention-to-treat basis. We will calculate cost of intervention, but will not carry out any specific health economic modeling in this phase II trial, since it would be premature to do so. We need first to establish whether this weight management can prevent weight gain, before assessing the combined effects of the weight gain prevented and the effects on cessation rates in a phase III trial.

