### Loss to follow-up

In accordance with the Russell Standard, we will conduct an intention-to-treat analysis and assume participants lost to follow-up are smokers. We will attempt to contact participants who do not attend. Reminder phone calls will also be made before 12-week and 6-month follow-up appointments.

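### The rule on data after the research team withdraws a participant from treatment appears to end data use at that point, which conflicts with the follow-up rule beside it and with the intention-to-treat analyses

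*Protocol article*

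**What the plan says.** The protocol article has two adjacent rules under Withdrawal criteria.

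- **Participant decision to withdraw.** Missing treatment visits does not count as leaving the trial: "these participants will still be contacted for follow-up appointments unless they have requested otherwise". The section separates stopping treatment from stopping follow-up.
- **Research team decision to withdraw.** The trigger is worded: "In the event that a participant develops a condition in which dietary energy restriction is ill-advised, for example embarking on a course of chemotherapy". Such a participant is withdrawn from treatment. The data rule follows: "Data up to the time of withdrawal from treatment will be used unless the participant requests otherwise". The section does not say whether follow-up visits continue.

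The analysis sections then state:

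- Secondary analysis: "Abstinence will be analysed on an intention-to-treat basis".
- Exploratory outcomes: their associations with weight control and quitting success "will be examined using regression modeling and on an intention-to-treat basis".
- Loss to follow-up: "we will conduct an intention-to-treat analysis and assume participants lost to follow-up are smokers".
- Primary analysis, which is not described as intention-to-treat: "Weight will be analysed in long-term abstainers because only long-term abstainers gain more weight over time than the rest of the population".

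**The concern.** The cut-off for data use is tied to the end of treatment, not to the end of follow-up or of consent. Under intention-to-treat, outcomes measured after treatment stops still count in the randomized arm. Two participants who both stop Slimming World in the same week would be handled differently, depending on whether they stopped attending or the team withdrew them.

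Twelve-week weight and abstinence are by definition measured at week 12. For anyone withdrawn before then, data up to withdrawal contain neither. That person would leave the abstainer-only weight comparison. For abstinence, the only rule the article offers for absent data is to count the person as a smoker.

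The losses would probably fall on one arm. The condition that triggers withdrawal is defined by its bearing on a restricted diet, and control advisors offer no such treatment: "they will not provide detailed or personalized advice on weight and will not set weight targets". The illnesses concerned can themselves plausibly change weight. The 12-week session is also meant to inform the sample size of the later non-inferiority trial (Session 7), so abstinence by arm matters beyond this trial.

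**Working it through.** **Step 1. The texts side by side**

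| Situation | Follow-up | Data used |
|---|---|---|
| Participant stops attending treatment | Continues unless they ask otherwise | No cut-off stated |
| Team withdraws participant from treatment | Not stated | Up to withdrawal from treatment |
| Abstinence, exploratory outcomes, loss to follow-up | – | Intention-to-treat |

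The second row does not fit with the first or the third unless post-withdrawal data are also used, and the sentence does not say that they are.

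**Step 2. The plan's own sample size**

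Inputs from Sample size: difference 2 kg, SD 2.5 kg, alpha 5% (sidedness not stated; two-sided assumed), power 90%, 20% abstinent at 12 weeks.

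- n per arm = 2 × [SD × (1.960 + 1.282) / difference]² = 2 × [2.5 × 3.242 / 2]² = 32.8, against the stated figure of about 32.
- 32 / 0.20 = 160 per arm, 320 in total, as stated.
- With 32 per arm: 2 / (2.5 × √(2/32)) = 3.20; 3.20 − 1.96 = 1.24; power = 0.893 (normal approximation).

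**Step 3. Size of the possible loss**

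The article gives no rate of team withdrawals. Its figure of under 5% is for participants who ask to leave, so it does not apply here. I assume a rate w of 1%, 2% or 5% in the Slimming World arm, all before week 12, with the same proportional loss among that arm's 32 expected abstainers and none in control.

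- Abstainers kept: m = 32 × (1 − w).
- Power = Φ[2 / (2.5 × √(1/32 + 1/m)) − 1.96].
- Apparent abstinence, if those withdrawn are counted as smokers: 20% × (1 − w).

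| w | Withdrawn of 160 | m | Power | Apparent abstinence, Slimming World arm |
|---|---|---|---|---|
| 0 | 0 | 32 | 0.893 | 20.0% |
| 1% | 1.6 | 31.7 | 0.891 | 19.8% |
| 2% | 3.2 | 31.4 | 0.889 | 19.6% |
| 5% | 8.0 | 30.4 | 0.885 | 19.0% |

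Based on the t distribution, power goes from 0.883 to 0.881, 0.880 and 0.875. Either way the fall is under 1 percentage point. Apparent abstinence falls by 0.2 to 1.0 points, with no matching fall in control under these assumptions.

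**The case against.** The strongest reply is that the sentence may only be about keeping data already collected. It does not say that later data are discarded or that follow-up stops. Weight and abstinence are measured at stop smoking and follow-up visits, not at Slimming World, so ending Slimming World does not cancel those visits. This stands in part: the exclusion is implied, not explicit. But a sentence that names an end point for data use, directly after a section that expressly preserves follow-up, will be read as a limit.

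Four stronger readings are tempting, and the article does not support them.

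- **That the rule applies only to the Slimming World arm.** The text speaks of a participant, and the duty to report a changed medical history covers everyone. The asymmetry is a sound inference from what each arm receives, not a stated rule. Nor does the article say how a control participant with the same illness is handled.
- **That those withdrawn will be counted as smokers.** That rule is written for people who do not report or are lost to follow-up. Extending it to this group is an inference.
- **That the primary weight analysis breaks an intention-to-treat promise.** It is limited to abstainers by design. For weight, the issue is possible differential loss.
- **That the weight result could be badly distorted.** One could imagine a control abstainer who changes by −8 kg instead of +2.5 kg, which moves the control mean by (−8 − 2.5)/32 = −0.33 kg. The −8 kg is invented, and conditions in which weight loss is contraindicated are already excluded at entry.

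The reply that an article leaves such detail to a fuller document does not remove the point. A data rule is stated here, and it clashes with other statements in the same article.

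**Conclusion.** The point holds as an inconsistency of low severity. On its natural reading, the sentence ends data use when the team stops treatment. That does not agree with the follow-up rule for non-attenders or with intention-to-treat for abstinence, for exploratory outcomes and under Loss to follow-up. Any loss would probably be concentrated in the Slimming World arm.

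The size is small: under 1 percentage point of power and 0.2 to 1.0 points of apparent abstinence. This rests on an assumed 1% to 5% withdrawal in one arm, on loss unrelated to abstinence, and, for the abstinence figure, on those withdrawn being counted as smokers. It does not measure bias in the weight difference, for which the article gives no basis. The planned 320 participants are unaffected. The matter is still worth settling in advance, because in an open-label trial it should not be decided once allocation and outcomes are known.

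**What to change.** Reword the data sentence under Research team decision to withdraw to say the following:

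- Withdrawal from treatment by the research team is not withdrawal from follow-up.
- In both arms, weight and abstinence will still be collected at the scheduled visits: 4 weeks, 12 weeks, and 26 weeks if that visit is held. It remains conditional on the 12-week result.
- These data will be used in the analyses by randomized arm, with the primary weight analysis still limited to abstainers.
- The exception is a participant who withdraws consent to follow-up.

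The clinical rule for when treatment is stopped is not touched. The cost is one or two sentences. The visits are already planned, and the sample size does not change.
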